## Abstract

Opportunistic testing using the prostate-specific antigen (PSA) test is common among men aged 75–79 yr. American and European guidelines consider PSA-based screening through joint decision-making if men have at least 10 yr of life expectancy. The age threshold for PSA-based screening was previously described in these guidelines as 70–74 yr. However, Swedish men, similar to their global counterparts, are experiencing increased life expectancy. As of 2024, Swedish men aged 75–79 yr have on average >10 yr of life expectancy. To date, there are no randomized controlled trials on prostate cancer screening for men aged 75–79 yr at baseline. With a lack of randomized data, we plan on leveraging the population-based Stockholm Prostate Cancer Diagnostics Register from 2007 to 2023, to explore the effect of PSA-based screening on all-cause and prostate cancer–specific mortality. In this target-trial emulation study protocol, our aim is to evaluate whether PSA-based screening in men aged 75–79 yr with no previous prostate cancer diagnosis would have survival benefits from PSA-based screening. We will conduct sequential and clone-censor-weight target-trial emulations based on the age at enrollment, assigning men to screened or unscreened arms based on the observational analog of an intention-to-screen analysis of PSA test records. Men will be followed until death or December 31, 2023. The statistical analysis involves survival models, reporting of the cumulative incidence functions (CIF), and differences in CIFs. Sensitivity analyses aim to evaluate whether similar findings can be observed if we restrict enrollment to those who have a minimum of 5 and 10 yr of follow-up, consider calendar year instead of age at enrollment, and consider enrollment of younger men. This study aims to provide evidence on the survival benefits of PSA-based screening in this age group, and clarify whether extending screening guidelines to men aged 75–79 yr would reduce mortality without exacerbating the risk of overdiagnosis. Findings will guide clinical recommendations and inform the design of future randomized controlled trials. The study is registered at ClinicalTrials.gov (NCT07206693).

## Introduction

1

Prostate cancer (PCa) screening allows for the early detection of potentially aggressive PCa cases to reduce mortality and morbidity [1]. Among Swedish men, PCa is the leading cause of cancer mortality, accounting for nearly fifth of all cancer deaths [2]. Currently, prostate-specific antigen (PSA)-based screening is available for men with life expectancy of ≥10 yr, provided that they understand the risks and benefits of PCa screening through a shared decision-making process [3]. Current European Association of Urology and American Urology Association guidelines suggest PSA-based screening up to ages 70 or 74 yr [3,4]. Despite these recommendations, PSA-based screening in men aged ≥75 yr is common [[5], [6], [7]]. As populations live longer [8], the number of older men with at least ≥10 yr of life expectancy is increasing. In 2024, Swedish men aged 75 yr had average life expectancy of 12.44 yr, while those aged 79 yr had average life expectancy of 9.74 yr [9]. With this trend, life expectancy might exceed 10 yr in men older than 79 yr in the near future. Therefore, fit men aged ≥75 yr could be considered for screening according to medical guidelines.

On the contrary, with increasing age, the number and complexity of chronic diseases increase [10]. Septuagenarians have heterogeneous health status declining with increased age [11]. Detection of PCa that is unlikely to metastasize or cause health issues might lead to unnecessary stress or worry, with health outcomes exacerbated negatively by the potential overtreatment [12]. Furthermore, if a PCa case is to be detected, the choice of radical or conservative therapy can have an impact on survival [[13], [14], [15]].

To address the dilemma of screening for PCa among older men, and to provide recommendations on who to test and when to stop screening, randomized controlled trials (RCTs) would provide the strongest evidence. However, even if an RCT were to be conducted specifically to address this gap, the long follow-up necessary for such an RCT to mature would delay the availability of evidence to make clinical and epidemiological recommendations. Moreover, there might be ethical concerns about conducting an RCT without demonstrated benefit leveraging observational data in alignment with the principle of equipoise [16]. The usage of large observational data to emulate a target trial can assist in bridging the gap and provide directions to inform future RCTs [17]. Emulation of target trials aims to address causal questions utilizing several statistical and epidemiological methods to capitalize on available observational data to reach potentially similar findings as RCTs conditional on the proper data structuring and data analysis in line of addressing the research question [[18], [19], [20], [21]].

Hence, in this protocol, we outline the study aims to address two research questions: (1) What are the characteristics of men aged 75–79 yr who are screened despite no clinical recommendations? (2) Utilizing a target-trial emulation, what is the impact of PSA-based screening on all-cause and PCa-specific mortality among men aged 75–79 yr?

## Methods

2

To address the aims of the study, an intention-to-screen analysis plan of a target-trial emulation will be conducted based on PSA testing among men aged 75–79 yr. The target-trial emulation protocol and study conduct will follow the guidelines and recommendations of Hernán et al [17,20].

### Hypothesis

2.1

Our hypothesis is that men aged 75–79 yr who are screened for PCa using PSA, despite no prior PCa diagnosis, gain a modest survival benefit by reducing PCa mortality through the detection and future treatment of lesions with metastatic potential.

### Study population and data source

2.2

This study and the target-trial emulation will use population-based register data of men living in Stockholm between 2007 and 2023, who were screened for PCa, extracted from the Stockholm Prostate Cancer Diagnostics Register (STHLM0), a comprehensive register of all men tested for PCa with PSA in Stockholm, Sweden [22]. The STHLM0 has complete PSA test records since January 1, 2007 [22]. This will be supplemented with information on nontested men from the STHLM0+ register [22]. Demographic information, family history of PCa, diagnoses, hospitalization, specialized outpatient health care, PCa treatment, and mortality information are provided from the linked Swedish population registers [22]. Figure 1 illustrates the flowchart of inclusion into the target-trial emulation.

**Fig. 1 f0005:**
[figure not shown]
Flowchart showing inclusion into and exclusion from emulated target trials. (A) The main analysis inclusion based on age. (B) The sensitivity analysis based on calendar year. Cloning refers to the duplication of each participant in the study, which is later assigned to one of the two screening strategies. PSA = prostate-specific antigen.

### Eligibility criteria

2.3

Men aged 75–79 yr between 2007 and 2023, with no PCa diagnosis at the time of inclusion (based on each trial emulation), will be considered eligible for the trials. To ensure proper control for potential confounding and to be able to evaluate the eligibility criteria, only men with complete information on their screening status, outcomes, and confounders in the registers will be included. The summary number of the men excluded due to missing values will be described in the final study flowchart.

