### Outcomes

2.8

The first outcome of interest is all-cause mortality, which will be based on the reported date of death. The second outcome of interest is PCa-specific mortality, which will be ascertained based on the leading cause of death. The International Classification of Disease tenth revision is used to report the cause of death, and the code C61 is used to identify PCa-specific mortality. Men who are alive by December 31, 2023 will be censored by reaching the end of the follow-up period.

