#### Data preparation and choice of confounders

2.10.1

Data on all men living in Stockholm will be used, and ascertainment of time zero will be performed for all eligible men with no information on the variables necessary for the analysis missing. As men can continuously be eligible to be included in the sequential trials, the choice of time zero will follow the recommendation of Hernán et al [17], and emulation will be done repetitively during the eligibility period between 2007 and 2023. The confounders of interest are age (continuous), trial year (categorical; from 2007 to 2023), country/region of birth (categorical; Sweden, Nordic, European Union, and others), income (categorical; five quintiles), previous hospitalization during the past year (yes/no), number of hospitalizations during the past year (continuous), number of outpatient specialized health care visits (continuous), non–age-adjusted Charlson Comorbidity Index (continuous, based on adaptations for register-based Swedish data [20], and cumulatively computed, based on the past 5 yr until the end of the previous calendar year before the assessment), education (categorical; ≤9 yr of formal education, 10–12 yr of formal education, and ≥12 yr of formal education), civil status (categorical; not married, married, divorced, and widowed), current cancer diagnosis excluding PCa (yes/no), and family history of PCa (yes/no, based on father, brother[s], or son[s] diagnosed with PCa).

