The actual capture of the outcome in PCa-specific mortality might be challenging to ascertain without autopsy among older men as the quality of the cause-of-death reporting decreases with age, and the death certificate might be suboptimal to capture PCa mortality among the oldest age group [[41], [42], [43]]. This observation has been reported in Nordic countries [42,44]. Thus, the sticky-diagnosis bias might affect determining whether PCa was the cause of death among the screened men compared with the nonscreened men [45]. As such, evaluation of both all-cause and PCa-specific mortality would be warranted, and this misclassification could affect PCa mortality, but not all-cause mortality [46]. A comparison of the risks among younger age groups can assist in ascertaining whether a potential difference in direction is due to the limitations of death certificates in older age and the sticky-diagnosis bias.

Although the study focuses primarily on mortality outcomes, diagnosis outcomes are addressed only descriptively, and the quality-of-life outcomes are not available in the registries. These findings would be needed for a fully informed decision-making process and subsequent updates to clinical guidelines.

Positivity is assumed as part of the emulation of target-trial design [47]. However, this might not be feasible in real life, as men who are very frail would be evaluated differently by health care providers and might not be considered for screening by the urologist as they might not be able to tolerate even conservative therapy.

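### Entry requires complete outcome information, which conditions inclusion on the future; the bias is of unknown and possibly small size, and a short wording change removes it

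*Protocol article*

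**What the plan says.** Section 2.3 (Eligibility criteria) sets the entry rule: "only men with complete information on their screening status, outcomes, and confounders in the registers will be included". The reason given is "To ensure proper control for potential confounding and to be able to evaluate the eligibility criteria". For the men removed, the plan provides only a count: "The summary number of the men excluded due to missing values will be described in the final study flowchart".

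Section 2.10.1 carries the rule to the start of follow-up: "ascertainment of time zero will be performed for all eligible men with no information on the variables necessary for the analysis missing".

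Section 2.8 defines the endpoints. The first is "all-cause mortality, which will be based on the reported date of death". The second is "PCa-specific mortality, which will be ascertained based on the leading cause of death", with ICD-10 code C61 marking a prostate cancer death. For survivors, "Men who are alive by December 31, 2023 will be censored by reaching the end of the follow-up period". Section 2.7 ends follow-up at the outcome or at the end of 2023 and names no other reason.

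Section 3.3 concedes that "the quality of the cause-of-death reporting decreases with age". It treats this as misclassification that can affect prostate cancer mortality but leaves all-cause mortality intact.

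**The concern.** A target trial fixes eligibility with what is known at enrolment. Here one of the conditions is the completeness of an event that may occur up to 17 years later. The two reasons given in section 2.3, confounding control and checking eligibility, need no outcome data.

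The condition is also one-sided. A man alive at the end of 2023 needs neither a date nor a cause of death, so his outcome record is complete by definition. Among men with full follow-up, only a man who died can fail. Section 2.3 states one rule for one cohort, so a death with a known date but no cause record would be removed from all-cause mortality as well, although section 2.8 needs only the date for that endpoint. All-cause mortality is the endpoint that section 3.3 relies on because it does not depend on the recorded cause, and the entry rule weakens that independence.

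Men whose vital status is lost are caught too. Sections 2.3 and 2.7 taken together exclude them altogether instead of following them to the date of loss.

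Nothing later in the plan corrects this. The weights in sections 2.10.2 and 2.10.4 address screening assignment and artificial censoring. The sensitivity analyses in section 2.11 do not relax the entry rule.

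**Working it through.** **Inputs.** From section 2.12: baseline cumulative mortality 0.80 after 17 years, 20% screened, 35 000 deaths, and Table 1. The share of deaths with an incomplete outcome record, *m*, is not in the document. It is an assumption throughout and is shown as a range.

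**The plan's own figure.** With Schoenfeld's formula and two-sided alpha 0.05 (assumed; the article does not state it), power is Φ(√(35 000 × 0.2 × 0.8) × |ln HR| − 1.96). For HR 0.956 this is Φ(74.83 × 0.0450 − 1.96) = Φ(1.41) = 92.0%, as in Table 1 for an absolute reduction of 1.5 points. The power figures do not bear on the entry rule. They give the scale of effect that the study is looking for: 1.0 to 3.0 points in Table 1, with 1.28 points stated as the minimum for 80% power.

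**Effect of the rule on one arm.** Take N men with true cumulative mortality *p*, all followed to the horizon (a simplification). Removing a share *m* of the deaths leaves pN(1 − m) deaths among N(1 − pm) men, so the observed risk is

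p(1 − m) / (1 − pm).

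For small *m* this falls by about p(1 − p) × m. At p = 0.80 that is 0.8 × 0.2 = 0.16 points per percentage point of *m*. As an exact check, m = 1% gives 0.792/0.992 = 0.7984, and m = 2% gives 0.784/0.984 = 0.7967, a difference of 0.16 points.

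**Effect on the contrast at 0.80 control mortality.** The reduction is control minus screened, in percentage points.

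| Assumed m, control / screened | Observed control mortality | True reduction 0 reads | True reduction 1.5 reads |
|---|---|---|---|
| 0 / 0 | 0.800 | 0.00 | 1.50 |
| 1% / 1% | 0.798 | 0.00 | 1.51 |
| 2% / 2% | 0.797 | 0.00 | 1.52 |
| 5% / 5% | 0.792 | 0.00 | 1.55 |
| 2% / 1% | 0.797 | −0.16 | 1.34 |
| 3% / 1% | 0.795 | −0.33 | 1.18 |
| 5% / 2% | 0.792 | −0.51 | 1.01 |
| 1% / 2% | 0.798 | +0.16 | 1.68 |

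Equal missingness lowers both curves and hardly moves their difference. Unequal missingness moves the difference, and the sign follows the arm that loses more deaths.

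**Dependence on the mortality level.** The factor p(1 − p) peaks at p = 0.5. There, 2% against 1% shifts the difference by 0.25 points and 3% against 1% by 0.51. At p = 0.40 the shift per 1-point gap is about 0.24 points. Shorter horizons with mortality near one half are therefore somewhat more exposed than the 17-year figure.

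**How large a gap would matter by itself.** For a spurious difference of 1.28 points at p = 0.80 with nothing missing in the other arm, m = 0.0128 / (0.80 × 0.2128) = 7.5%.

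**What the arithmetic leaves out.** It covers removed deaths and all-cause mortality only. For prostate cancer mortality the direction depends on the true causes of the dropped deaths. Excluding men lost while alive discards event-free time, which pulls the estimate the other way; the documents give no figure from which to size it.

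**The case against.** The strongest reply is that poor cause-of-death quality is not missing outcome information. Under section 2.8 a prostate cancer death is one coded C61. A death with a vague or wrong code is simply not C61, and its outcome is recorded. Only a death with no cause record at all could fail the rule, and the documents do not suggest that such deaths are common. This stands, and it limits the size of the problem.

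A reader might go further and infer that both mortality endpoints are distorted in a known direction: screened men are diagnosed more often, their deaths are better documented, fewer of them are dropped, and the contrast shifts against screening. The documents do not support this. Section 3.3 describes misclassification and attribution to a known diagnosis, not absent records. No missing fraction is given for either arm.

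The design also works against a large gap. Men are cloned into both strategies and re-enter monthly from age 75 to 79 (sections 2.5 and 2.10.2), so a man removed for his outcome record usually leaves both arms. The two-arm table above ignores this and so overstates the shift for a given gap between screened and unscreened men.

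It can also be said that section 2.10.1 speaks of the variables needed for the analysis, which could be read endpoint by endpoint, so that a missing cause would not affect all-cause mortality. That reading is possible, but section 2.3 states the rule without this qualification. The flowchart count would show an appreciable loss, though it would not correct it.

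Finally, a condensed article may leave censoring at emigration to a fuller plan. That silence alone would be no finding. The point on lost men stands only because section 2.3 states that men with incomplete outcomes are not included.

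**Conclusion.** The rule as written conditions entry on post-baseline information, and the stated reasons for it do not require that. This holds on the text alone. Dropping deaths understates cumulative mortality in both arms by an unknown amount, which is small if the registers are nearly complete.

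The difference in cumulative incidence is biased materially only if missingness differs by arm. At the plan's 0.80 mortality the shift is about 0.16 points per 1-point gap, before dilution by men contributing to both arms. This rests on an assumed *m*, full follow-up to the horizon, and arms treated as separate groups of men. The sign is not established.

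The point merits correction as a should-fix, because the error is structural and cheap to remove. The documents do not show a distortion large enough to make it a must-fix.

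**What to change.** - In section 2.3, delete outcomes from the completeness criterion. In section 2.10.1, limit completeness to variables known at or before time zero.
- Count every death with a known date as an all-cause event, whatever the state of the cause record.
- In the prostate cancer mortality analysis, keep deaths with no cause record as deaths from other causes, and add one bounding run that counts them as prostate cancer deaths.
- In section 2.7, censor at loss of register coverage instead of excluding the man.

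The cost is a few sentences of wording and one extra run. A small number of deaths of uncertain cause stay in the prostate cancer analysis, and the bounding run shows how much they matter.

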### Screening strategy

2.4

Two types of target-trial emulations are proposed, with both aimed to address the second research question but using different causal inference methods. Two different methods are performed to evaluate whether the results would agree, giving confidence to the conclusions made based on the findings of the study. The first method employs a sequential design and the clone-censor-weight (CCW) approach with enrollment/inclusion based on the attained age (main analysis). The second method performs the analysis based on the calendar year (sensitivity analysis). The CCW approach handles time-varying eligibility and treatment assignment while avoiding the immortal time bias, and the sequential design enables repeated trial emulation at multiple entry points to maximize generalizability and emulate real-world decision-making [20,21].

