### Main analysis—sequential design with the CSW approach based on age at enrollment

2.5

Emulated target trials assign men into one of the two screening arms based on their screening pattern during the eligibility period, which starts when they attain the age of interest for the study (75–79 yr) for the first time and every month thereafter (eg, at age 75 yr, 75.083 yr, 75.167 yr, and so on).

Screening is ascertained within the 1st month from trial initiation, representing the eligibility and assignment period. Eligible men with at least one PSA test in this period will be assigned to the screening arm. Those with no PSA test in this window will be assigned to the control arm. Assignment ascertainment is assumed to be accurate for all participants, as the STHLM0 contains the data on PSA testing for men living in Stockholm and who were tested in Stockholm since 2007 [22]. Considering the assumptions of causal inference frameworks [19], the following three principles are assumed to be fulfilled:1.Positivity: Every man living in Stockholm within the age group of interest has a nonzero chance of deviating from the protocol at any point during the assessment period, and every eligible man is assumed to have had the opportunity to undergo a PSA test.2.Consistency: The survival outcome we observe for the men under the given screening strategy is the same as the outcome that would have occurred if we had explicitly assigned these patients to follow the same strategy (ie, their potential outcome). As such, the screening protocol is assumed to have been defined clearly and applied consistently throughout the study period in our study. Moreover, we assume that the statistical models used in the analysis (described below) are specified correctly.3.Exchangeability: There are no unmeasured confounders; all factors that influence both the screening assignment and the likelihood of deviating from the protocol have been measured. We assume based on the confounders accounted for in the study (described below) that we address the potential factors that impact the screening assignment.

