#### Analysis based on calendar year

2.11.1

Emulated target trials with observational analog of an intention-to-screen analysis will be conducted, using the CCW method and sequential design every month in alignment to the main analysis. However, the month’s assessment will start from January 1, 2007. Men are ascertained for their screening within the month if they are eligible (75–79 yr). The intervention arm includes eligible men screened with PSA for PCa, while the control arm includes eligible men not screened for PCa during that specific month period. Follow-up starts on January 1, 2007 and ends on December 31, 2023, or when mortality occurs, whichever comes first.

Figure 1B illustrates the flowchart of the inclusion into the trial based on the sensitivity analysis.

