#### Other sensitivity analysis considerations

2.11.2

In addition to the different causal inference methods, this study will consider limiting the recruitment period to December 2018 and December 2013 to allow for longer follow-up time among eligible men. We will consider extending the ascertainment period of the PSA-based screening to 12 mo instead of 6 mo. A deterministic sensitivity analysis for unmeasured confounding using the array method, as described by Schneeweiss [26], will be performed, and the curved surface representing the “fully” adjusted ratio based on the assumed prevalence and varied strength of the unmeasured confounder will be plotted. Moreover, the results will be contrasted with men aged 65–69 and 58–62 yr (in contrast to men aged 75–79 yr).

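### The calendar-year analysis is the main analysis on a shifted monthly grid, so agreement shows robustness to the grid only, and its single follow-up start date conflicts with section 2.7

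*Protocol article*

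**What the plan says.** Section 2.4 introduces two emulations, "both aimed to address the second research question but using different causal inference methods". Their agreement is to carry inferential weight: "Two different methods are performed to evaluate whether the results would agree, giving confidence to the conclusions". The first is described as follows: "The first method employs a sequential design and the clone-censor-weight (CCW) approach with enrollment/inclusion based on the attained age (main analysis". The second is based on calendar year and is tagged a sensitivity analysis. Section 2.11.2 repeats the label when it opens its further checks with "In addition to the different causal inference methods".

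Section 2.11.1 defines the second emulation as "using the CCW method and sequential design every month in alignment to the main analysis". What it changes is the grid: "However, the month’s assessment will start from January 1, 2007. Men are ascertained for their screening within the month if they are eligible (75–79 yr". It then states: "Follow-up starts on January 1, 2007 and ends on December 31, 2023, or when mortality occurs, whichever comes first".

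Section 2.7, which governs follow-up, starts each man's follow-up at inclusion and lets time zero depend on the design, but spells time zero out only for the main analysis (the date the age is attained).

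**The concern.** Agreement between two analyses supports a conclusion only against errors that the two do not share. If the second uses the same men, exposure rule, adjustment set, weights and outcome model, a bias in the first reappears essentially unchanged in the second, and concordance is close to built in.

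This matters because section 3.3 says that functional status, overall health status and disability are not in the registers, and that very frail men may not be considered for screening. Healthier men being tested more often is thus a leading threat to the all-cause mortality comparison, and the calendar-year analysis is not sensitive to it. Section 3.1 expects the results to inform guidelines, so the stated grounds for confidence should be ones the design can deliver.

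The follow-up sentence is a separate problem. A single start date for a sequence of trials running to 2023 would, if programmed as written, create time before assignment in which a man could not have died. Section 2.4 says the chosen approach avoids exactly that.

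**Working it through.** **1. The two analyses side by side**

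| Element | Main analysis | Calendar-year analysis |
|---|---|---|
| Method | Sequential design with clone-censor-weight (2.4, 2.5) | The same (2.11.1) |
| Trial frequency | Monthly (2.5) | Monthly (2.11.1) |
| Population | Age 75–79 yr, 2007–2023, no prostate cancer (2.3) | Same age window (2.11.1); no variant of 2.3 |
| Which tests count as screening | 2.6 | No variant stated |
| Confounders | 2.10.1, one list containing both age and trial year | No variant stated |
| Weights and survival model | 2.10.2, 2.10.4 | No variant stated |
| Outcomes | 2.8 | No variant stated |
| Where months begin | On reaching the age range, "for the first time and every month thereafter (eg, at age 75 yr, 75.083 yr, 75.167 yr, and so on" | 1 January 2007 onward |
| Start of follow-up | Date of age attainment (2.7) | 1 January 2007 (2.11.1) |

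Only the last two rows differ. Age and trial year are both adjusted for already, so moving from one grid to the other does not change the adjustment set.

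**2. How far the grids can differ**

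The plan's last recruitment age is 79.91 yr. Monthly trials from age 75 give 75 + 59/12 = 79.92 yr for the 60th, which reproduces that figure to within rounding, so a man has up to 60 monthly trials. On either grid his windows are one month long and cover the same age span. Their starting points differ by less than one month, so only edge months at entry, exit and the study limits can drop out.

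An illustrative simulation puts a size on this. Its assumptions, none of them figures from the plan, are:
- 20 000 men, with 75th birthdays uniform over the months that give some eligibility in 2007–2023
- 60 eligible months per man
- PSA tests Poisson at about 20% per year
- no deaths or diagnoses

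Results:
- Person-trials: 920 101 on the age grid and 924 699 on the calendar grid. Ratio 924 699 / 920 101 = 1.005.
- Share of all tests falling in an age-grid trial 99.5%, in a calendar-grid trial 99.2%, in both 98.7%.

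**3. The follow-up start, read literally**

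There are 17 × 12 = 204 calendar-month trials. Number them j = 0 to 203. With follow-up fixed at 1 January 2007, trial j has j months of follow-up before its assignment month begins.
- Trials affected: 203 of 204.
- Mean lead over trials, unweighted: (0 + 203)/2 = 101.5 months. Maximum: 203 months.
- On that clock no death can occur before 5 yr in trials with j ≥ 60, which is 204 − 60 = 144 trials (71%).
- The same holds at 10 yr for 204 − 120 = 84 trials (41%), and at 15 yr for 204 − 180 = 24 trials (12%).

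The cumulative incidences and their differences at 5, 10 and 15 yr planned in section 2.10.4 would then no longer measure time since assignment. With time zero at the start of each calendar month, the lead is 0 in every trial.

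**The case against.** The case for leaving this alone has several parts.

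- **The analysis is already labelled a sensitivity analysis.** This is true in section 2.4, in the heading of 2.11, in the Figure 1 caption and in the Abstract. Regrouping by calendar month is a legitimate, if narrow, check. This stands. What remains wrong is the description as a different causal inference method and the inference drawn from agreement.
- **The follow-up sentence is shorthand.** Section 2.7 starts follow-up at inclusion, and 2.11.1 says it runs in line with the main analysis, so the sentence probably describes the study window. The added time is also common to both arms of a trial. This largely stands. A reader might infer that the calendar-year analysis will suffer immortal-time bias, but the documents do not show that. They show two passages that conflict. Time common to both arms would still displace the cumulative incidences at fixed horizons.
- **Confounding has its own checks.** Section 2.11.2 plans an array analysis for unmeasured confounding and a contrast with younger men, section 2.10.5 restricts by comorbidity, and all-cause and prostate-cancer mortality are reported side by side. This stands too. A reader might infer that shared bias would pass unnoticed, or recur identically in both analyses. Neither is supported: an all-cause difference far larger than the prostate-cancer difference would be visible in the planned output, and the grids are not exactly the same. However, none of these checks makes the claim in 2.4 valid. The array analysis depends on an assumed prevalence and strength of the confounder, and section 3.3 gives the younger-age contrast a different purpose (death-certificate quality and sticky-diagnosis bias).
- **The figures cannot be seen.** Figures 1A and 1B might show a further difference between the inclusion flows. The text of 2.11.1 describes none beyond the grid and the follow-up start.

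A reader might also want a threshold above which an all-cause difference must be confounding. The documents give prostate cancer's share of cancer deaths but not its share of all deaths at these ages, so no such threshold can be derived.

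**Conclusion.** The concern holds in two limited parts.

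First, sections 2.4 and 2.11.2 describe as a different causal inference method something that 2.11.1 defines as the same method on a grid shifted by less than one month per man. Agreement supports robustness to that shift. It adds little against unmeasured confounding, misclassified test intent or model misspecification. This conclusion rests on comparing the sections. The 98.7% overlap illustrates it and depends on the simulation assumptions.

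Second, the fixed start date in 2.11.1 conflicts with 2.7. Taken literally it affects 203 of 204 trials; taken as drafting it affects none. It should be reconciled, and it is not evidence of a biased analysis.

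Neither part invalidates the main estimate. The change should be made because a stated ground for confidence is unsound and because time zero in an emulated trial should be unambiguous.

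**What to change.** - **Sections 2.4 and 2.11.2:** replace the description as different causal inference methods with a sensitivity analysis on the time grid, and say that agreement speaks to the choice of grid only.
- **Section 2.11.1:** set time zero at the start of each calendar-month trial, consistent with 2.7, and give 1 January 2007 to 31 December 2023 as the study window.
- **Low-cost addition:** report the non-prostate-cancer mortality difference in cumulative incidence at 5, 10 and 15 yr, with the same weights, as a negative-control outcome beside the planned array analysis. If the cumulative incidences treat other deaths as competing, it is close to the gap between the two differences already planned.

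The first two changes are wording only. The third is at most one more outcome run, since causes of death are already linked. Its weakness is that cause-of-death misclassification and sticky-diagnosis bias (section 3.3) can move deaths between the two categories without any confounding. It should therefore be read as a diagnostic and not as a formal rule for attributing an all-cause difference to screening.
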